## Assessment schedule and follow up

Study assessments will be conducted at baseline, 6-months, 12-months and 18-months. Each study assessment will involve participants:

1. attending the body composition laboratory for an assessment;
2. attending a local pathology collection centre for a blood test;
3. wearing two activity monitors over seven (7) days (and returning monitors via post);
4. completing two telephone interviews;
5. completing a questionnaire.

| **Time point:** | **Hospital recruitment** | **Screening/ recruitment** | **Baseline assessment**  **(BL)** | **6-month assessment**  **(6M)** | **12-month assessment**  **(12M)** | **18-month assessment**  **(18M)** | **Early Termination** |
| --- | --- | --- | --- | --- | --- | --- | --- |
| **Inclusion criteria** | x |  |  |  |  |  |  |
| **Consent to contact** | x |  |  |  |  |  |  |
| **Informed consent** |  | x |  |  |  |  |  |
| **Exclusion Criteria** |  | x |  |  |  |  |  |
| **Case report forms** |  | x |  |  |  |  | x |
| **Randomisation/allocation** |  |  | x |  |  |  |  |
| **Body composition assessment** |  |  | x | x | x | x |  |
| **Blood sample collection** |  |  | x | x | x | x |  |
| **Activity monitor wear** |  |  | x | x | x | x |  |
| **Telephone interview** |  |  | x | x | x | x |  |
| **Questionnaire** |  |  | x | x | x | x |  |
| **Adverse events** |  |  |  | x | x | x |  |
| **Participant satisfaction (Intervention only)** |  |  |  |  | x |  |  |

At baseline, participants must complete the body composition assessment, have a blood sample taken, complete the physical activity measurement (wearing the hip and thigh monitors) and telephone interviews in order to be randomised into the study. Whilst it is desirable for participants to also complete the self-report questionnaire, and this will be encouraged, this data is not essential and participants can be randomised even if this is incomplete. Participants who fail to complete all the essential assessment components will not be randomised into the study.

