## Withdrawal criteria

Participants will be withdrawn from the study if they report any of the following during the course of the study:

- Cancer recurrence or new cancer diagnosis
- Contraindications to participating in unsupervised physical activity, dietary or weight loss program (mobility issues, recent heart attack or angina, breathing difficulties requiring hospitalization or oxygen use, use of warfarin, pregnancy) – *Note: if a participant becomes pregnant during the course of the study, they may continue to receive intervention calls if they wish, with their doctor's approval*
- Moving interstate/overseas and therefore unable to complete study assessments

Participants are free to withdraw from the study at any point. If an intervention participant indicates that they wish to withdraw from the study they will be given the opportunity to withdraw from the intervention (and not receive any further telephone calls) but continue to complete the study assessments or to withdraw from the study completely and no complete any further intervention calls or study assessments.

Participants who choose to withdraw completely from the study will be asked to provide a reason for withdrawing which will be documented in the study database. Following this, participants will receive no further contact in relation to the study. Data collected from participants up until the point of withdrawal will be kept in the study database and used in data analysis. The study target sample size of 160 participants allows for attrition and therefore additional participants will not be recruited to replace withdrawing participants.

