# Safety reporting

Adverse events (AEs) will be assessed for all participants at each follow-up assessment (6-, 12- and 18-month). In addition, all participants will specifically be asked about unintended weight loss (i.e. weight loss greater than expected based on changes made to physical activity and dietary intake). All AEs will be recorded on a standard Adverse Event Report Form (appendix k) and submitted to the chief investigator.

The chief investigator will determine the severity and relationship of the AE to the intervention and take appropriate action(s). Severity will be graded from 1 (mild) to 5 (fatal) based on the National Cancer Institute’s Common Terminology Criteria for Adverse Events (CTCAE) classification. The attribution of the AE to the intervention will be determined to be unrelated (unrelated or unlikely) or related (possible, probable or definite). AE Report Forms for participants reporting unintended weight loss will be reviewed by the CI in consultation with CI [name] (Medical Oncologist) to determine the appropriate course of action. The chief investigator will submit AE Report Forms to the Safety Monitoring Committee, which will oversee the monitoring of trial safety and AEs reporting for the study. The Committee will consist of three members including a cancer clinician and two behavioural scientists. The Chair of the committee will have appropriate experience or training in trial safety. All AEs will be reported to the chair of the committee, with serious AEs that may be related to the intervention reported within 48 hours of notification. The committee will meet via teleconference as needed.

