# Statistical methods

## Sample size and justification

### Power for primary endpoints

The sample size calculation is based on observing an average weight loss in the intervention group at the end of the intervention (12-months) of 7% of initial body weight[[30](#_ENREF_30)] and allowing for a small regain in weight in the intervention group from 12- to 18-months (+1.2%)[[31](#_ENREF_31)] and small changes in weight among the control group (approx ±1%).[[15-18](#_ENREF_15)] Thus, we expect that weight loss from baseline to 18-months follow-up, expressed as percent of initial body weight, will be at least 5% greater in the intervention group compared to the usual care group**.** Assuming a standard deviation of change of 8.5%[[16](#_ENREF_16)] and allowing 25% attrition at 18-months,[[32](#_ENREF_32)] 80 women per group (160 participants in total) will be needed to detect this minimum difference in weight loss between groups with 90% power and a type I error of 5% (two-tailed).

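### Adverse events are not asked about when a woman withdraws completely, so events since her last six-monthly assessment go unsolicited, and one who leaves before month 6 is never asked at all

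*Protocol*

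**What the plan says.** Three parts of the Protocol settle when adverse events are asked about.

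- **Section 5.6, schedule table.** The adverse-event row reads "Adverse events | | | | x | x | x", with marks at 6, 12 and 18 months. The last column, Early Termination, is empty in that row. Its only mark is in the row "Case report forms | | x | | | | | x".
- **Section 6, Safety reporting.** The text agrees with the table: "Adverse events (AEs) will be assessed for all participants at each follow-up assessment (6-, 12- and 18-month". It adds that every participant is asked specifically about unintended weight loss.
- **Section 4.3, Withdrawal criteria.** A woman who chooses to leave completely "will be asked to provide a reason for withdrawing which will be documented in the study database". The next sentence closes the file: "Following this, participants will receive no further contact in relation to the study". An intervention participant may instead "withdraw from the intervention (and not receive any further telephone calls) but continue to complete the study assessments".

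Section 8.1.1 sizes the trial "allowing 25% attrition at 18-months".

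**The concern.** Withdrawal is the last moment at which a woman can be asked about harm, and the plan already includes a contact then. That contact asks only why she is leaving. An injury or illness since her last assessment reaches the safety data only if she volunteers it.

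For a woman who leaves in the first six months there is no earlier assessment to fall back on. That period holds 16 of the 22 planned calls (section 5.3.1: 6 weekly plus 10 fortnightly, then 6 monthly) and the start of the exercise programme. She would never be asked either safety question, although section 6 says that all participants are.

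What is at stake is how complete the adverse-event data are. The protocol grades events, attributes them to the intervention and sends them to a Safety Monitoring Committee. The gap falls just before women leave, and some may leave because they are hurt or unwell. An analysis plan cannot recover answers that were never sought.

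**Working it through.** **1. Does any other section fill the gap?**

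| Possible route | What the Protocol says | Does it elicit events at exit? |
|---|---|---|
| Case report forms marked at Early Termination (5.6) | Section 9.3 describes forms for data from the study assessments and gives no adverse-event content for exit | Not stated |
| Coaching calls (5.3.1) | Content is progress, problem-solving, advice, goals and an action plan | No; intervention arm only |
| Rapid reporting (6) | "with serious AEs that may be related to the intervention reported within 48 hours of notification" | No; it passes on events already notified |
| Reason for withdrawal (4.3) | Asked and documented | Only if the event is given as the reason |
| Stopping calls but keeping assessments (4.3) | Follow-up visits continue | Yes, at the next visit, so these women are not affected |

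No section provides an adverse-event enquiry at complete withdrawal.

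**2. Inputs for scale**

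- Sample size: 160, 80 per group (section 8.1.1).
- Attrition: 25% at 18 months (section 8.1.1).
- Follow-up: 18 months, with adverse events asked about every 6 months (sections 5.6 and 6).
- Timing of exits: not given, so assumed below.

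**3. The plan's own figure.** With a difference of 5, an SD of 8.5, two-sided 5% and 90% power, the normal approximation gives n = 2 × (1.96 + 1.2816)² × 8.5² / 5² = 60.7, so 61 completers per group. Then 61 / 0.75 = 81.3, so 82 per group against the stated 80. Taking 80 × 0.75 = 60 completers, power is 89.7%. The stated size is reproduced to within 2 women per group, so 25% can be read as loss from the 160 randomised.

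**4. Women affected, upper bound.** 0.25 × 160 = 40.

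**5. Time not asked about**

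- Planned follow-up: 160 × 1.5 = 240 woman-years.
- Maximum, if every leaver goes just before her next assessment: 40 × 0.5 = 20 woman-years; 20 / 240 = 8.3%.
- Exits even within each six-month interval, a mean gap of 3 months: 40 × 0.25 = 10 woman-years; 10 / 240 = 4.2%.

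**6. Women never asked at all** (those who leave before month 6)

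- Exits even over 18 months: 40 × 1/3, about 13 women.
- Assuming that 20% to 60% of leavers go before month 6: 40 × 0.2 = 8 to 40 × 0.6 = 24 women.

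These counts take all 40 as voluntary complete withdrawals, so they too are ceilings under each timing assumption.

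**The case against.** The strongest reply is that the protocol contains no contradiction: table and safety text agree, section 8.2 says the trial has no safety endpoints, and events can still surface. Section 6 has all adverse events put on a report form, and its rule for serious related events runs from notification, so reports need not wait for a visit. The event that drives a woman out is also the one she is most likely to name. This stands in part. A reader might infer that nothing is recorded for a woman who leaves. The text supports only that nothing is solicited. The content of the exit form is not shown either, so it may hold more than the protocol says.

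A reader might also infer that the under-count makes the intervention look safer, since only intervention women can leave because of the programme. The protocol does not establish this. Intervention women have frequent calls in which to volunteer an event, usual-care women have no comparable contact, and all events count whether related or not. The imbalance could run either way.

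Nor does the protocol say that early leavers would be counted as event-free. It states no adverse-event denominator, which may properly be left to the analysis plan.

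Finally, section 8.1.1 does not break down the 25%. It may include women withdrawn by rule under section 4.3, whose reported condition is itself the trigger, and women lost without any exit contact. So 40 is a ceiling, not an estimate.

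None of this supplies an adverse-event question at exit.

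**Conclusion.** The point holds in a limited form. Followed as written, the schedule leaves adverse events unsolicited from the last assessment to exit for every woman who withdraws completely by choice. A woman who does so before month 6 is never asked about adverse events or unintended weight loss. Ascertainment is therefore incomplete and may differ between arms, in an unknown direction.

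The size is modest: at most 40 women and 20 of 240 planned woman-years (8.3%), or about 10 woman-years (4.2%) if exits are even within intervals. These figures assume that all planned attrition is voluntary and complete; the true number is likely to be smaller. The time share is small, but it is the time just before leaving. The sample size and primary analysis are unaffected. This is a cheap improvement to the safety data, not a threat to the trial's main result.

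**What to change.** - In the section 5.6 table, mark Adverse events under Early Termination.
- In sections 4.3 and 6, state that at the contact where the reason for withdrawal is asked, the standard adverse-event questions, including the one on unintended weight loss, are put to every woman in either arm who is willing to answer. They should cover the time since her last assessment, or since baseline if she has had none.

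Women who stop only the calls need no extra enquiry. They are asked at their next visit, and an added question for them would apply to one arm only.

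The cost is one table cell, a sentence in each of two sections, and a few minutes per withdrawing woman at a contact already planned. No visit is added. Some women will decline or be unreachable, so the gap will narrow but not close. The answers would also inform the review of reasons for drop-out in section 8.5.

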## Allocation method

Participants will be allocated to either the Intervention group of the Usual Care group following completion of baseline data collection. A staff member who does not work on the study will create a computer-generated randomisation plan using uneven block sizes ([www.randomization.com](http://www.randomization.com)). This staff member will be notified when participants have completed baseline assessment and will allocate the participant IDs to either the usual care group or the intervention group based on the randomisation plan.

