### 5.6.1 Body Composition Assessment

The first component of each assessment to be completed is the Body Composition Assessment. The Body Composition Assessment is to be completed at the Body Composition Laboratory at the Royal Children’s Hospital. A laboratory technician, with the appropriate accreditation will conduct the assessment (appendix g).

The following data will be collected:

- Self-reported pre-diagnosis weight
- Height (stadiometer)
- Weight (digital scales)
- Waist circumference (non-expandable tape at top of iliac crest)
- Hip circumference (non-expandable tape at widest point of the buttocks)
- Blood pressure (Omron T8)
- Whole-body and segmental body composition - fat mass, fat-free mass (Lunar Prodigy DEXA scanner)
- Bone mineral density – hip and lumbar spine (Lunar Prodigy DEXA scanner)
- Physical functioning – hand grip strength (Smedley handheld dynamometer); timed chair stands (5 sit-to-stand repetitions)

At this assessment, participants will be provided with the pathology request form for the blood sample collection and two 5ml SST tubes to take with them to the Sullivan Nicholaides Pathology (SNP) Collection Centre, the activity monitor pack (including the hip and thigh monitors and express postage return pack), a food model booklet for use in the telephone interviews and the self-report questionnaire (with reply-paid envelope).

Body composition and bone mineral density will be measured by a DEXA machine. Having a DEXA scan done is similar to having an x-ray but has about 10% of the radiation of a chest x-ray.

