### 5.6.5 Questionnaire

The self-administered questionnaire collects information on patient reported outcomes (quality of life, fatigue, body image, menopausal symptoms, fear of cancer recurrence, arthralgia, peripheral neuropathy) and a range of constructs related to social-cognitive theory as well as sleep and depression, which will be examined to assess whether they mediate or moderate the relationship between the intervention and the primary and secondary outcomes (appendix i). The specific instruments included in the questionnaire are (version 3, amended 20/08/13):

- Outcome Expectancy for diet and physical activity – Diet items modified from Zunft et al., 1997; PA developed based on Rodgers & Brawley, 1991 & Williams et al., 2005
- Satisfaction with diet and physical activity outcomes – Developed for study based on outcome expectancy items
- Self-regulation for diet and physical activity – Modified from Petosa, 1993
- Self-efficacy for diet and physical activity – Diet modified Linde Barriers-based Self-Efficacy (for diet & PA) scale; PA modified Marcus et al., 1992
- Social support – Sallis Social Support for Eating & Exercise scales
- Perceived environmental opportunity for healthy eating and physical activity – Healthy eating modelled from Disdall et al., 2005 & Moore et al., 2008; Physical activity modified IPS-E, Inoue et al., 2008
- Sleep disturbance – Insomnia Severity Index (Q1-5)
- Quality of life – PROMIS Global Health Scale
- Fatigue – FACT-IT
- Depression – PROMIS SF-Depression 1.0
- Body image – PAL Relationships and Body Image Scale
- Menopausal symptoms – Greene Climacteric Scale
- Fear of cancer recurrence – Concerns about Recurrence Questionnaire (CARQ-4)
- Arthralgia (Breast Cancer Prevention Trial Musculoskeletal Pain Subscale)
- Peripheral neuropathy (Patient Neurotoxicity Questionnaire (PNQ))

The questionnaire is available for completion in either hard-copy (given to all participants attending for their Body Composition Assessment) or electronic format (LimeSurvey platform, hosted on the Faculty of Health Sciences secure server).

All intervention participants will also be given a short satisfaction questionnaire to complete at the end of the program (after 12-months) (appendix j). This questionnaire will ask about their overall satisfaction with the program, satisfaction with particular components, areas of participation they found difficult and suggestions for improvements to the program.

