## Secondary outcomes

- Physical activity
- Dietary intake
- Waist and hip circumference
- Body composition and bone mineral density
- Blood pressure
- Clinical biomarkers of metabolic health: glucose, lipids, HbA1c, insulin, leptin, adiponectin, C Reactive Protein
- Genomic and DNA Methylation-based biomarkers
- Patient-reported outcomes: quality of life, fatigue, body image, menopausal symptoms, fear of cancer recurrence
- Cost-effectiveness

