### 8.3.2 Statistical analyses for secondary outcomes

Similar models will be performed for each secondary outcome, using the baseline value of the outcome as a covariate.

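### Women can be randomised without the baseline questionnaire, yet each patient-reported outcome model needs its baseline score, and the protocol sets no rule for a missing score or a late form

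*Protocol*

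**What the plan says.** Protocol section 5.6 (Assessment schedule and follow up) requires the body composition assessment, blood sample, activity monitoring and telephone interviews before a woman can be randomised: "Participants who fail to complete all the essential assessment components will not be randomised into the study". The questionnaire is encouraged but exempt: "this data is not essential and participants can be randomised even if this is incomplete".

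Section 5.6.5 describes what the form is for: "The self-administered questionnaire collects information on patient reported outcomes". Section 7.2 lists five of these as secondary outcomes: "Patient-reported outcomes: quality of life, fatigue, body image, menopausal symptoms, fear of cancer recurrence". Section 8.3.2 sets the analysis: "Similar models will be performed for each secondary outcome, using the baseline value of the outcome as a covariate".

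On timing, section 5.2 places allocation "following completion of baseline data collection". Section 5.6.1 has the form handed out at the body composition visit, to be returned by post. Section 5.6.5 also offers an electronic version. Section 5.4 leaves participants unblinded once allocated. Section 8.5 leaves the handling of missing data to a later choice among a completers analysis, multiple imputation and selection models.

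**The concern.** The protocol lets a covariate be absent at randomisation and then requires it in five outcome models. A likelihood-based mixed model copes with missing responses but not with a missing covariate. Unless a further step is specified, women who were randomised and who returned every follow-up questionnaire can leave the analysis of an outcome because one earlier form was missing.

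Two things are at stake. The first is precision, and how well the analysed women represent those randomised. The second is whether the covariate is a true baseline. A form completed after the woman knows her arm, or after coaching calls have started, may already reflect allocation, and adjusting for it can bias the estimated group difference. The exploratory moderator analyses share this second problem where the moderator comes from the same form, as fear of cancer recurrence does (sections 5.6.5 and 8.3.5).

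**Working it through.** **1. The passages side by side**

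| Item | Weight (primary) | Five patient-reported outcomes |
|---|---|---|
| Baseline source | Body composition assessment (5.6.1) | Self-report questionnaire (5.6.5) |
| Required before randomisation (5.6) | Yes | No |
| Baseline value used as covariate | Yes (8.3.1) | Yes (8.3.2) |
| Covariate can be missing for a randomised woman | No | Yes |

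**2. What the stated model does.** Sections 8.3.1 and 8.3.2 together describe, for woman *i* at follow-up visit *j*:

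Y_ij = b0 + b1·group_i + b2·time_j + b3·(group_i × time_j) + b4·Y_i0 + error_ij

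If the baseline score Y_i0 is missing, the right-hand side is undefined at 6, 12 and 18 months alike, so all three follow-up rows are unusable unless Y_i0 is imputed or the model is rewritten.

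**3. The protocol's own sample size.** Inputs from section 8.1.1: difference 5, SD 8.5, two-sided 5% error, 90% power, 25% attrition.

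- n per group = 2 × [8.5 × (1.960 + 1.282) / 5]² = 60.7, that is 61.
- Inflated for attrition: 60.7 / 0.75 = 81.0, or 82 from the rounded 61. The protocol states 80.
- With 80 × 0.75 = 60 analysed per group, power = Φ(5/8.5 × √(60/2) − 1.960) = 89.7%. The protocol states 90%.

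The primary calculation reproduces within rounding and is not in dispute. The power claimed in section 8.1.2 for quality of life and body image cannot be checked, because no difference or SD is given.

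**4. Illustrative loss of precision.** The protocol gives no rate of missing baseline questionnaires, so the shares below are assumptions. Take an outcome with exactly 80% power at 60 analysed women per group. The standardised difference is d = (1.960 + 0.842) × √(2/60) = 0.511. Remove a share *m* from each arm: power = Φ(d × √(60(1 − m)/2) − 1.960).

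| Assumed share missing | Analysed per group | Power |
|---|---|---|
| 0% | 60 | 80.0% |
| 5% | 57 | 78.0% |
| 10% | 54 | 75.7% |
| 15% | 51 | 73.3% |

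Starting from 80 per group (d = 0.443) gives the same powers, since only the fraction kept matters.

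**5. The timing gap.** Section 5.2 puts allocation after baseline collection. Section 5.6 allows it while the questionnaire is outstanding. The form is at home or online, the woman learns her arm, and no section says when a form ceases to count as baseline. Keeping data collectors blinded (5.4) does not protect a form that the participant fills in herself.

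**The case against.** A reader might infer that women without the form must either be dropped or be given a baseline completed after allocation. The protocol prescribes neither. Section 8.5 names multiple imputation, and section 8.3.3 promises sensitivity analyses under different missing-data assumptions, so a route that keeps these women lies within the plan. This stands against the stronger reading. It does not close the gap: section 8.5 frames missingness as drop-out, lists a completers analysis on equal terms, and never mentions a missing baseline score in a woman who is fully followed up.

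Post-allocation completion is likewise an inference. The form is handed out at the first baseline component, and seven days of monitor wear and two interviews must follow before randomisation, so many forms may be back in time. What remains is that nothing excludes a late one.

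The handling of missing covariates is often left to a SAP, and none is shown. Silence alone would not be a finding. Here, though, the protocol itself fixes both the exemption and the covariate, and the two do not fit together.

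The size is also open to challenge. An incomplete form may still yield some of the five scores. Women who skip it may be the same women who later drop out, so the losses could overlap. Section 8.1.2 claims at least 80% power, not exactly 80%, and only quality of life and body image among the five have that claim. The others fall in its 50% to 80% band. All of this stands, and it means the power figures are illustrations only.

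Finally, not letting a questionnaire block enrolment into a weight-loss trial is a defensible choice, and the fix leaves it in place.

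**Conclusion.** The point holds for the five patient-reported secondary outcomes. The stated model cannot use a woman with no baseline score, and the protocol fixes neither how such a score is handled nor which forms count as baseline. Baseline weight comes from an essential assessment, so the primary outcome is untouched.

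Missingness that arises before allocation mainly costs precision and representativeness; by itself it does not bias the comparison between arms. The cost is about 2 to 7 percentage points of power, on three assumptions: 5% to 15% missing equally in both arms, exactly 80% power beforehand, and exclusion of every affected woman. Bias between arms would come chiefly from forms completed after allocation, and the documents give no basis for saying how often, or whether, that would occur. This is a worthwhile and inexpensive clarification and does not threaten the trial's main conclusion.

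**What to change.** For the questionnaire outcomes, replace the baseline-as-covariate model with a constrained longitudinal model: baseline is one of the repeated responses, with a common mean in both arms, and group differences are estimated at 6, 12 and 18 months. This keeps every randomised woman with any measurement. An acceptable alternative is to keep the covariate and pre-specify imputation of the missing baseline score without using allocation.

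In either case, count a questionnaire as baseline only if it was completed on or before the date of allocation, and otherwise set the baseline score to missing. Apply the same date rule to moderators taken from the form, and align section 5.2 with section 5.6 on which components must be complete before allocation.

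The cost is a model statement, a little more analysis work and a date check. The check needs a recorded completion date. The questionnaire itself (appendix i) is not shown, so whether one is already captured should be confirmed. No extra assessment is needed, and no woman is refused randomisation over the form.
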